#### Secondary outcome

2.7.2

**The Chinese version of the Nepean Dyspepsia Symptom Index (NDSI)** The NDSI is a validated dyspepsia-specific questionnaire that quantifies the severity of 15 upper gastrointestinal symptoms in patients with FD over the past 14 days (24). Each symptom is assessed along three dimensions: frequency, intensity, and degree of interference with daily activities. The higher the NDSI total score, the more severe the dyspeptic symptoms are. During the study, NDSI scores were measured at weeks 1, 5, 9, 13, and 17.

**The Chinese version of Short Form-Nepean Dyspepsia Life Quality Index (SF-NDLQI)** The SF-NDLQI instrument is an FD-specific 10-item questionnaire that assesses the impact of upper gastrointestinal symptoms on QOL across 5 domains: tension, interference with daily activities, eating/drinking, knowledge/control, and work/study (25). Each domain has two items, and each item is scored from 1 to 5, with lower scores better quality of life. In this study, the SF-NDLQI will be administered at weeks 1, 5, 9, 13, and 17.

**The Chinese version of the Hospital Anxiety and Depression Scale (HADS)** The HADS will be employed to evaluate the anxiety and depressive symptoms of patients. This scale consists of 7 items for anxiety (HADS-A) and 7 items for depression (HADS-D), with each item scored from 0 to 3, resulting in a total subscale score range of 0 to 21 (26). Higher scores reflect greater levels of anxiety or depression (27). The HADS has demonstrated strong reliability and validity in screening for anxiety and depression among general medical patients (28). Assessments utilizing the HADS will be conducted at weeks 1, 5, 9, 13, and 17.

**Acupuncture expectation** The Expectation for Treatment Scale (ETS), developed by Jürgen Barth and his colleagues, will be utilized to evaluate patients’ acupuncture expectations before treatment (29). This scale comprises 5 items, such as “I anticipate that the treatment (acupuncture) will alleviate my complaints.” Each item is rated on a scale from 1 to 4, representing partial disagreement, partial agreement, agreement, and definite agreement, respectively. The total score ranges from 5 to 20. A higher total scale score indicates a greater expectation of achieving positive clinical outcomes. The ETS will be measured at week 1.

**Laboratory tests** Serum levels of motilin, gastrin, and ghrelin will be measured using enzyme-linked immunosorbent assays. Fasting venous blood samples (2 mL) will be collected at baseline and after 4 weeks of treatment from all study participants and stored at −80°C until analysis. Laboratory tests will be performed by trained laboratory professionals blinded to treatment assignment.

### Safety

2.8

AEs are pivotal in evaluating the safety of treatments. All AEs, whether linked to the study treatment (acupuncture or itopride), will be recorded in the case report form (CRF). Each AE will be comprehensively described, including start/stop dates and times, severity, relationship to treatment, actions taken, and the necessity for treatment discontinuation. Researchers will closely monitor all AEs until they are resolved. In the case of serious AEs (e.g., events leading to disability, impaired ability to work, or life-threatening situations), immediate reporting will be made to both the academic center and ethics committee. If any severe AEs associated with acupuncture arise, the ethics committee has the authority to consider suspending the trial.

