**Discussion:**

In conclusion, this trial will determine the efficacy and safety of acupuncture for PDS and provide more high-level evidence to support its application in treating FD.

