### Intervention

2.6

This trial consists of a screening phase (1 week), a treatment phase (4 weeks), and a post-treatment follow-up phase (12 weeks). During the treatment period, participants in the verum acupuncture plus placebo group will receive 12 sessions of verum acupuncture treatment and itopride placebo tablets for 20 days. Patients in the itopride plus sham acupuncture group will take itopride tablets for 20 days and receive 12 sessions of sham acupuncture treatment. Patients in the sham acupuncture plus placebo group will take itopride placebo tablets for 20 days and receive 12 sessions of sham acupuncture treatment. The detailed treatment procedures is as follows:

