### Outcome

2.7

Primary outcomes in this study include the proportion of responders (PR) and the elimination rate of the main symptom. The secondary outcomes include changes in symptom score, QOL, mood during the treatment and follow-up, and the participants’ expectancy for acupuncture before treatment, as well as related hormone concentrations. Table 2 display a summary of all measurements. Follow-up for all participants can be completed via social media (WeChat) or phone.

**Table 2 tab2:** SPIRIT figure for the schedule of enrollment, interventions, and assessments.

	Study period								
	Enrolment	Allocation	Treatment phase				Follow-up		
Timepoint**	*1w*		*2w*	*3w*	*4w*	*5w*	*9w*	*13w*	*17w*
Enrolment									
Eligibility screen	X								
Informed consent	X								
Allocation		X							
Interventions									
Verum acupuncture plus placebo									
Itopride plus sham acupuncture									
Sham acupuncture plus placebo									
Assessments									
Proportion of responders			X	X	X	X	X	X	X
Elimination rate			X	X	X	X	X	X	X
NDSI		X				X	X	X	X
SF-NDLQI		X				X	X	X	X
HADS		X				X	X	X	X
Acupuncture expectation		X							
Related hormone concentrations		X				X			
Adverse events			X	X	X	X			

SPIRIT, standard protocol items: recommendations for interventional trials; NDSI, the nepean dyspepsia symptom index; SF-NDLQI, the short form - Nepean Dyspepsia Life Quality Index; HADS, Hospital Anxiety and Depression Scale.

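### Section 2.8 promises to record all adverse events without an end date, but Table 2 schedules no adverse event assessment after week 5, so events that begin in the 12-week follow-up have no planned point of ascertainment

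*Protocol article*

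**What the plan says.** Section 2.8 (Safety) is open-ended on what is recorded: "All AEs, whether linked to the study treatment (acupuncture or itopride), will be recorded in the case report form (CRF"). I read this as covering events whether or not they are related to treatment. For each event it asks for a full description: "Each AE will be comprehensively described, including start/stop dates and times, severity, relationship to treatment, actions taken". On follow-up of events it says: "Researchers will closely monitor all AEs until they are resolved". No date or visit is given at which collection stops.

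Table 2 (section 2.7, Outcome) is the schedule of assessments. Its row labelled "Adverse events" carries four marks, at weeks 2, 3, 4 and 5. The cells at weeks 9, 13 and 17 are empty.

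Section 2.6 (Intervention) gives the periods: "This trial consists of a screening phase (1 week), a treatment phase (4 weeks), and a post-treatment follow-up phase (12 weeks"). Section 2.7 gives the mode of the later contacts: "Follow-up for all participants can be completed via social media (WeChat) or phone".

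Safety is a stated aim. The abstract says that "this trial will determine the efficacy and safety of acupuncture for PDS", and section 2.1 describes the trial as a comparison of efficacy and safety between acupuncture and itopride. Section 2.12 plans a descriptive summary of AEs between groups and states no time window.

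**The concern.** The text and the schedule differ in scope. Section 2.8 covers every event with no time limit, while the schedule asks about events only up to the end of treatment. Nothing in the article says that AE collection is confined to the treatment weeks, so the reader cannot tell which of the two governs.

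The practical risk concerns events that begin after week 5. Staff who follow Table 2 would contact the participant three more times, complete the efficacy measures, and have no prompt to ask about new events. Such an event would reach the case report form only if the participant raised it. One centre might ask and another might not, which would make the later AE data uneven across the three hospitals. The AE summary could then be read as covering 16 weeks when it was gathered systematically over 4.

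**Working it through.** The article states no figure on this point, so there is none to reproduce. The check is an alignment of Table 2 with its header, a comparison with section 2.8, and one ratio.

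**Step 1. Align the rows of Table 2.** The header columns after allocation are weeks 2, 3, 4, 5, 9, 13 and 17.

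| Row | 2 | 3 | 4 | 5 | 9 | 13 | 17 |
|---|---|---|---|---|---|---|---|
| Proportion of responders | X | X | X | X | X | X | X |
| Elimination rate | X | X | X | X | X | X | X |
| NDSI | | | | X | X | X | X |
| SF-NDLQI | | | | X | X | X | X |
| HADS | | | | X | X | X | X |
| Adverse events | X | X | X | X | | | |

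The HADS row is marked at weeks 5, 9, 13 and 17, which agrees with the HADS times in section 2.7.2. The columns are therefore read correctly, and the blanks in the AE row are not an effect of text extraction.

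**Step 2. Count the scheduled AE assessments.** They occur at 4 of the 7 time points after allocation and at 0 of the 3 follow-up contacts. Five efficacy measures are marked at each of those three contacts.

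**Step 3. Express the gap in time.** Section 2.6 gives 4 weeks of treatment and 12 weeks of follow-up. With week 1 as screening, treatment ends at week 5 and the last contact is at week 17.

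- Span after treatment starts: 4 + 12 = 16 weeks
- Span after the last scheduled AE assessment: 17 − 5 = 12 weeks
- Share without scheduled AE assessment: 12 / 16 = 75%

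**Step 4. Compare with section 2.8 by type of event.**

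| Type of event | Section 2.8 | Table 2 | Result |
|---|---|---|---|
| Begins by week 5 and resolves by week 5 | Recorded | Assessment scheduled | Consistent |
| Begins by week 5 and is open at week 5 | Followed to resolution, stop date recorded | No later contact marked for it | Commitment stands; the contact is not named |
| Begins after week 5 | Within the scope of all AEs, no end date | No assessment scheduled | Mismatch |

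Only the third line is a real mismatch between the two places. The second is a matter of clarity.

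**The case against.** The strongest reply is that the two places answer different questions. A schedule of assessments shows when staff ask about events; the text says what is done with an event once it is known. Both can hold together: planned questions through week 5, with identified events followed until they resolve. Collecting AEs over the weeks in which needling and tablets are given is also a defensible design, and an article may leave the exact reporting window to the full protocol.

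Part of this stands. A reader might infer from the blank cells that events still open at week 5 are lost. The documents do not support that, because section 2.8 requires monitoring to resolution and stop dates, and an empty cell does not cancel a duty stated in the text. A reader might also infer that nothing at all is recorded after week 5. That too goes beyond the documents: section 2.8 puts no cut-off on recording and asks for immediate reporting of serious events without a time limit, so a volunteered event would still fall under it. What is missing is scheduled ascertainment.

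The reply does not dispose of events that begin after treatment. Both the open-ended wording and the schedule are printed in the article, and they differ in scope. This is a mismatch between two printed statements, so it is not simply a detail left to a fuller document. If on-treatment collection is intended, the article does not say so.

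**Conclusion.** The point holds for events with onset after week 5. They come under the wording of section 2.8, yet Table 2 gives no occasion to ask about them in 12 of the 16 weeks after treatment starts, or at any of the three follow-up contacts. Events open at week 5 remain covered by section 2.8; for them, the only shortcoming is that no contact is named at which the follow-up is done.

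The consequence is limited to how complete and how even the safety summary is over follow-up. The documents give no rate of late events, so the number that might go unrecorded cannot be estimated, and 75% describes time without scheduled assessment, not a share of events missed.

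The conclusion rests on two assumptions: that Table 2 is the operative schedule at the sites, and that no unseen document sets a different AE window. It is a minor point, worth settling because safety is a stated aim.

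**What to change.** Reconcile section 2.8 and Table 2. There are two ways to do it.

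- **Preferred:** mark the AE row at weeks 9, 13 and 17. At each of these contacts, by WeChat or phone as already planned, ask every participant in all three arms about new events and about any event still unresolved. In section 2.12, summarise on-treatment and post-treatment AEs separately by arm.
- **Alternative:** state in section 2.8 that AE collection is limited to the treatment period, name how and when events open at week 5 are followed, and limit the safety conclusion to the treatment period.

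The preferred route costs three marks in the table, one question at contacts that already exist, and one line in the analysis section. Its downside is small: some events unrelated to treatment will be recorded and must be classified. The alternative costs a sentence or two but gives up systematic safety information over the 12 weeks of follow-up. Either change is a protocol modification, which section 2.10 requires the ethics committee to approve.

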### Data collection and management

2.9

Clinical observers will complete a CRF for each participant to record all relevant clinical information. A dedicated data manager will then convert the paper-based CRF data to electronic format, with a secondary check by another research assistant to ensure data accuracy. Participants’ personal information will be anonymized and replaced with code for confidentiality during data collection. All data will be kept confidential, with electronic data secured on a password-protected server and paper data stored in locked cabinets. Access to clinical data will be restricted to authorized researchers only. Raw data will be retained for 5 years. The clinical inspectors/monitors will supervise the data collection and control for data completeness and quality.

### Quality control

2.10

Before the study begins, the research center will provide standardized training sessions for the entire research team to ensure they follow the study protocol and become familiar with the administration process. Clinical researchers are encouraged to contact the academic center for assistance if any technical or other issues arise at the clinical site. The academic center should promptly provide practical guidance to address these issues. Registered acupuncturists with a minimum of 5 years of experience will perform the acupuncture treatment. These acupuncturists will undergo training and testing before the trial to ensure consistency in their acupuncture operation. A two-level quality inspection system will be established to ensure the implementation and quality of program. Inspectors at each center will conduct monthly quality examinations, while an independent monitoring team will carry out quality monitoring every 3 months. After each quality inspection, quality control reports should be submitted to the research center. Furthermore, any modifications to the research protocol must receive approval from the ethics committee.

### Sample size calculation

2.11

The sample size for this study was determined based on the responder proportion at the end of a 4-week treatment, with 70.69% for the acupuncture treatment and 55.46% for the itopride treatment, as reported in a previous study (30). The sample size calculation was performed using PASS 15.0 software, with a 1:1 ratio between the verum acupuncture plus placebo group and itopride plus sham acupuncture group. A statistical power of 80% (*β* = 0.2), a one-sided alpha of 0.025 (*α* = 0.025), and a non-inferiority margin of −10% (*Δ* = −10%) were considered in the calculation. The resulting sample size was 57 for each group. Accounting for a 15% dropout rate, each group needed 67 cases, resulting in a total enrollment of 201 cases across three groups.

### Statistical analysis

2.12

Efficacy analyses will be performed on all patients who were randomized, adhering to the intention-to-treat principle. This approach ensures that all patients are included in the analysis based on the group to which they were initially assigned, regardless of whether they completed the study as intended. Missing data on the primary outcome will be imputed using the multiple imputation method under the missing at-random assumption. If there are significant differences in baseline variables between the two groups, those unbalanced variables will be included as covariates in the analysis of the primary outcome.

We will establish confidence intervals at a 95% level, with a significance level set at 0.05. Continuous data will be reported as mean ± standard deviation (SD) if it is normally distributed. Otherwise, it will be reported as median (interquartile range). For longitudinal continuous data, we will compare groups using repeated-measures analysis of variance (ANOVA), taking into account both group and time-group interactions. Student’s t-test or Wilcoxon rank-sum test will be used for other continuous data. For categorical data, Χ^2^ test or Fisher’s exact test will be applied as appropriate. The strength of linear relationships between variables will be evaluated using linear correlation analysis, and sensitivity analysis will be performed if required. The occurrence of AEs between groups will be summarized using descriptive analysis.

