#### Primary outcome

2.7.1

**The proportion of responders (PR)** Patients experiencing sufficient alleviation of stomach discomfort are categorized as positive responders (23). Participants will be requested to evaluate changes in their symptom relief over the preceding 7 days via a 7-point Likert scale. This scale features options such as “extremely worsened,” “worsened,” “slightly worsened,” “no change,” “slightly improved,” “improved,” or “extremely improved,” which correspond to scores ranging from 0 to 6. Those participants who report a relief score of either 5 or 6 points will be deemed positive responders. The measurement of PR will take place at weeks 2, 3, 4, 5, 9, 13, and 17.

**The elimination rate (ER)** ER refers to the proportion of patients whose main symptoms have disappeared. According to Rome IV criteria, we define postprandial fullness and bloating as the main symptoms. Included patients should have at least one of these symptoms. Using a 7-point Likert scale, the main symptoms are considered to have disappeared if the rating drops to 0 after treatment. ER will be measured at weeks 2, 3, 4, 5, 9, 13, and 17.

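### The tests named for the binary primary outcomes do not fit the planned multiple imputation, 95% intervals and covariate adjustment, or the −10-point non-inferiority margin

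*Protocol article*

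**What the plan says.** Section 2.7.1 defines two binary primary outcomes. For PR: "Those participants who report a relief score of either 5 or 6 points will be deemed positive responders". For ER: "ER refers to the proportion of patients whose main symptoms have disappeared".

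Section 2.12 then makes these commitments:

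- Analysis set: "Efficacy analyses will be performed on all patients who were randomized, adhering to the intention-to-treat principle".
- Missing data: "Missing data on the primary outcome will be imputed using the multiple imputation method under the missing at-random assumption".
- Intervals: "We will establish confidence intervals at a 95% level, with a significance level set at 0.05".
- Covariates, if baseline variables differ significantly between groups: "those unbalanced variables will be included as covariates in the analysis of the primary outcome".
- Categorical data: the chi-square "test or Fisher’s exact test will be applied as appropriate".

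Section 2.11 bases the sample size on PR at the end of the 4-week treatment. It uses a non-inferiority margin of −10% at one-sided 0.025 for acupuncture against itopride.

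The article names no effect measure or model for a binary outcome.

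**The concern.** Multiple imputation produces several completed data sets, and their results have to be combined. The usual route, Rubin's rules, needs an estimate and its variance from each set. A chi-square test delivers a statistic and Fisher's test only a p-value. Neither, as a test, delivers an estimate with a standard error, an interval, a covariate-adjusted result or a comparison with −10 points. The section promises the interval and the adjustment, and the sample size presupposes the margin comparison. A statistician who kept to the named tests could not deliver these without adding a method that the article does not mention.

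With 15% dropout planned, about 10 of 67 patients per arm may need imputed outcomes (0.15 × 67 = 10.05), so how the imputed results are combined can decide the conclusion.

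**Working it through.** **Inputs from section 2.11.** Response rates 70.69% (acupuncture) and 55.46% (itopride), margin 10 points, one-sided alpha 0.025, power 80%, 57 per group, 15% dropout, 67 per group.

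**1. The plan's own figure.** With unpooled variance,

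n = [p₁(1−p₁) + p₂(1−p₂)] × (1.960 + 0.842)² / (p₁ − p₂ + 0.10)²

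= (0.2072 + 0.2470) × 7.849 / 0.2523² = 56.0

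The unrounded value is 56.006, which rounds up to the stated 57. Dropout: 57/0.85 = 67.06, against the stated 67. The figure reproduces, and it belongs to a comparison of a risk difference with −10 points.

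**2. Commitments set against the named tests.**

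| Commitment | Chi-square | Fisher's exact |
|---|---|---|
| Pooling over imputations | Possible by the D2 approximation, test only | No standard rule |
| 95% interval | Not from the test | Not from the test |
| Covariates | No | No |
| Comparison with −10 points | No, tests no difference | No, tests no difference |

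**3. What the margin row means for power** (planned rates, normal approximation). Standard error with 57 per arm: √(0.4542/57) = 0.0893.

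- Margin comparison: Φ(0.2523/0.0893 − 1.960) = 0.807. With 67 per arm it is 0.865.
- Test of no difference, two-sided 5%: 0.390 with 57 per arm and 0.446 with 67. It would need 157 per arm for 80% power.

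**4. One illustrative data set.** Assumed, one random seed: 57 of 67 observed per arm, 40 and 32 responders, 10 missing per arm. There were M = 50 imputations, each drawing an arm's response rate from Beta(x + 0.5, n − x + 0.5) and then its missing outcomes.

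- Rubin's rules: total variance T = W + (1 + 1/M)B, where W is the mean within-imputation variance and B the variance between the imputed risk differences. Pooled risk difference 0.133, standard error 0.090, 95% CI −0.043 to 0.310, p = 0.139.
- D2 rule: with r = (1 + 1/M) × the variance of the square roots of the chi-square statistics, F = [mean chi-square − ((M+1)/(M−1))r]/(1 + r) = 2.14, p = 0.144.
- Separate imputed tables: chi-square p from 0.012 to 0.478; Fisher p from 0.019 to 0.595.

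The two pooled p-values agree. Only the first route gives an interval: its lower limit of −4.3 points lies above −10, so these data would show non-inferiority. The D2 result reports only that no difference was detected, which cannot be read as non-inferiority.

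**5. Error rates by simulation.** 67 per arm, 15% missing completely at random, 20 proper imputations; ranges are over repeated runs.

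| Handling | Equal rates of 55.46%, nominal two-sided 5% | True difference −10 points, nominal one-sided 2.5% |
|---|---|---|
| One completed data set, no pooling | 8.4–8.8% | 4.4–5.1% |
| Median of 20 p-values | 6.9–7.0% | not run |
| D2-pooled chi-square | 4.9–5.4% | not applicable |
| Rubin-pooled risk difference | 5.3–5.8% | 2.6–2.8% |

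For scale, the simulation error at 5% with 8,000 replicates is √(0.05 × 0.95/8000) = 0.24 points.

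At the planned rates, the 20 p-values fell on both sides of 0.05 in about half of simulated trials (49% for Fisher, 51% for chi-square). This shows why a combining step is needed. It is not an error rate of the plan.

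**The case against.** The strongest reply has three parts.

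**A valid pooled result exists.** A reader might infer that the named tests leave the all-randomised analysis with no single valid result. The documents do not support that. Chi-square statistics can be pooled by D2 with about the correct level. The 2×2 table in each imputed data set also yields a risk difference with a variance. At 67 per arm and rates of 55% to 71%, chi-square rather than Fisher would be the appropriate choice for PR. ER might have sparse cells, but the article gives no ER rate. This part stands in full.

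**The inflated error rates describe a misuse that the plan does not state.** A reader might infer that the trial's false-positive rate is 8% to 9%. Section 2.12 specifies multiple imputation, and combining across imputations is part of that method. Nothing tells the statistician to test one completed table or to average p-values. This also stands, so the inflation figures are conditional.

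**The article is condensed.** The imputation model, number of imputations and combining rule may sit in an analysis plan that is not shown, so their absence is no finding. The sentence on categorical data is generic and does not name PR or ER. The promised intervals and covariates suggest that an estimate-based analysis was intended. This stands in part. The article does not leave the method open, because it names tests. The intervals and covariates show what was intended but do not supply a method, and neither named test delivers them or the margin comparison.

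**Conclusion.** The point holds as a mismatch within the article. The chi-square and Fisher's exact tests are the only methods named for binary data, and they do not deliver the promised 95% intervals, the covariate adjustment or the comparison with −10 points. Under multiple imputation, Fisher's test has no standard pooling rule, and chi-square can be pooled only into a test of no difference.

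The clearest measure of what is at stake is power: 39% for a no-difference test against 81% for the margin comparison, with 57 per arm at the planned rates. The inflation to about 8–9% (nominal 5%) or 4–5% (nominal 2.5% at the −10-point boundary) would occur only if completed data sets were tested without proper pooling. It is not a property of the plan as written.

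The simulated figures assume 15% missing in each arm, unrelated to outcome. The worked data set shows feasibility and predicts nothing about the trial. This is a cheap improvement, not an error that invalidates the design.

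**What to change.** In section 2.12, replace chi-square/Fisher for PR and ER with the following:

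- In each imputed data set, estimate the risk difference and its standard error, for example from a logistic model with arm, institution and any adjustment covariates, marginally standardised.
- Combine these by Rubin's rules into one estimate and one 95% interval.
- For acupuncture against itopride, compare the lower limit with −10 percentage points. The lower limit of a two-sided 95% interval corresponds to the one-sided 0.025 in section 2.11. That section states the margin for the responder proportion, so the text should say whether it also applies to ER.
- Keep chi-square/Fisher for categorical tables that are not imputed.

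The cost is a few sentences and slightly more analysis work, with no extra patients or data. The change should be made before unblinding.

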### Randomization, allocation, and concealment

2.4

A research assistant at each clinical institution will conduct random assignments independently from other study activities. Eligible patients will be randomly assigned into the verum acupuncture plus placebo group, itopride plus sham acupuncture group, and sham acupuncture plus placebo group in a 1:1:1 ratio. A professional statistician will utilize SAS software (v9.3) to produce a list of random numbers stratified by clinical institution using block sizes of 6 or 9. The randomization process will be carried out through an online central randomization system. The randomization number and group assignment provided to each patient by the randomization system will be unique and unchangeable, ensuring fairness in treatment allocation.

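### Covariates for the primary analysis are chosen by baseline significance tests, a rule that leaves the adjustment to chance and would almost never pick up institution, the randomisation stratum

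*Protocol article*

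**What the plan says.** Section 2.12 (Statistical analysis) makes adjustment of the primary outcome conditional on baseline tests: "If there are significant differences in baseline variables between the two groups, those unbalanced variables will be included as covariates". It names no covariate that enters regardless of the data. For categorical data, which both primary outcomes are (section 2.7.1), it names the chi-square test or Fisher's: "exact test will be applied as appropriate". It sets 95% confidence intervals, "with a significance level set at 0.05".

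Section 2.4 (Randomization, allocation, and concealment) has the statistician "produce a list of random numbers stratified by clinical institution using block sizes of 6 or 9", for three arms at 1:1:1. No section of the article brings institution into an analysis.

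Section 2.11 (Sample size calculation) sizes verum acupuncture against itopride for non-inferiority on the difference in responder proportions, with a margin of -10 percentage points.

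**The concern.** Allocation is by a central randomisation system, so a significant baseline difference is a chance event. It says nothing about whether the variable predicts response. A rule driven by baseline p-values therefore has three weaknesses:

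- The primary model is not fixed in advance. Whether the result is adjusted, and for what, depends on the draw.
- It selects on the wrong property. A strongly prognostic variable with a moderate imbalance is left out, while an irrelevant one with a large imbalance is brought in.
- It works against the design. Stratified blocks hold institution in balance, so a test for imbalance will hardly ever select it. Yet a stratification factor is normally carried into the analysis, because an analysis that ignores it overstates the variance when sites differ in response.

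At stake are the precision of the confidence interval that is set against the margin, and a primary analysis that can be stated before the data are seen.

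**Working it through.** **Inputs.** From section 2.11: responder proportions "with 70.69% for the acupuncture treatment and 55.46% for the itopride treatment", margin -10 points, one-sided alpha 0.025, power 80%, dropout 15%, 57 per group before and 67 after dropout. From section 2.4: three institutions as strata, blocks of 6 or 9. From section 2.12: significance level 0.05, assumed here to apply to the baseline tests because no other level is given. Assumed, because the article gives no figure: the number of baseline variables, the spread of response between sites, and the correlation of a covariate with outcome.

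**1. The plan's own sample size.** With unpooled variance, n = [0.5546 × 0.4454 + 0.7069 × 0.2931] × (1.960 + 0.842)² / (0.10 + 0.1523)² = 56.006, rounded up to 57. Then 57 / 0.85 = 67.06 (stated as 67) and 3 × 67 = 201. The stated figures are reproduced and do not depend on the covariate rule.

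**2. How often the rule would act.** For k independent baseline variables tested at 0.05 in one two-group comparison, P(at least one enters) = 1 - 0.95^k:

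| k | P |
|---|---|
| 5 | 22.6% |
| 8 | 33.7% |
| 10 | 40.1% |
| 15 | 53.7% |
| 20 | 64.2% |

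The symptom, quality-of-life and mood scores are likely to be correlated, which lowers these figures.

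**3. What the rule would miss.** The largest standardised difference that is still non-significant with 67 per arm is 1.96 × √(2/67) = 0.34 SD.

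**4. Whether the rule could select institution.** A block of 9 holds three patients per arm, so an incomplete last block leaves two arms at most 3 apart at a site. Take near-equal sites with 24 v 21, 21 v 24 and 22 v 22 (67 v 67). The chi-square statistic is 4 × 1.5² / 22.5 = 0.40 on 2 degrees of freedom, against a critical value of 5.99. Selection is close to impossible.

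**5. Effect of testing first and adjusting second.** Simulation of 100,000 trials, 67 per arm, one normal covariate, continuous outcome, two-sided 0.05:

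| Correlation with outcome | Type I error, test then adjust | Type I error, always adjust |
|---|---|---|
| 0.3 | 0.046 | 0.049 |
| 0.5 | 0.042 | 0.049 |

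The departure is on the conservative side.

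**6. Effect of leaving institution out.** Simulation of 200,000 trials, 67 per arm, three near-equal sites (22, 22, 23), the same risk difference at each site, 95% confidence interval set against -10 points. With equal arms within sites, weighting by site size is the same as Mantel-Haenszel weighting. Each cell gives unstratified v stratified; power is at the stated rates.

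| Assumed spread of control rates between sites | One-sided type I error | Power |
|---|---|---|
| none | 0.026 v 0.026 | 86.0% v 85.8% |
| ±10 points | 0.024 v 0.025 | 86.4% v 87.0% |
| ±20 points | 0.020 v 0.025 | 87.4% v 90.2% |
| ±25 points | 0.016 v 0.026 | 88.4% v 92.2% |

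The unstratified analysis loses a little when sites differ by ±10 points, visibly more at ±20 or beyond, and nothing when they are alike.

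**The case against.** The strongest reply is that this is a condensed article and that an analysis plan not shown may carry institution into the model. That stands for institution taken alone, since silence is not a decision against it. It does not rescue the covariate rule, which the article states outright and which an analysis plan consistent with the protocol would have to follow.

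Several stronger readings are tempting, and the article does not support them:

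- **That the rule inflates false positives or lets the result be chosen.** The simulations show conservative error rates. Section 2.5 blinds the statisticians and puts unblinding after the analysis, which limits selection.
- **That baseline symptom score and treatment expectation go unused.** The NDSI is analysed as a repeated secondary outcome, and the expectation scale is a listed secondary measure (section 2.7: "The ETS will be measured at week 1"). Either could also enter through the rule itself. They are only not fixed as primary covariates.
- **That the primary test is switched silently.** The rule announces the adjustment openly. Which regression carries it may be left to the analysis plan.
- **That the reference to two groups is a separate error in a three-arm trial.** It can be read as the pair sized in section 2.11. Naming the pair would settle it.
- **That an unadjusted imbalance below 0.34 SD biases the result.** Under randomisation the unadjusted comparison remains valid. What is lost is precision.

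It is also fair to say that all three sites are traditional Chinese medicine hospitals recruiting Changsha residents, so a wide spread between them is not a given.

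**Conclusion.** The point holds as a poorly chosen, stated rule with modest consequences. It leaves the primary model open until the data are seen: a 23% to 64% chance of some adjustment for 5 to 20 independent variables at 0.05, and less with correlation. It leaves prognostic imbalances up to about 0.34 SD unadjusted, and it would almost never bring in institution.

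The likely cost is conservative. Type I error is 0.042 to 0.046 against a nominal 0.05 for testing first and adjusting second. At an assumed ±20-point site spread, one-sided type I error is 0.020 against 0.025 and power 87.4% against 90.2%. If sites are alike, leaving out institution costs nothing.

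These sizes rest on assumed numbers of variables, site spreads and correlations. The test-then-adjust figures come from a continuous outcome with one covariate, so for this trial's binary outcomes they show direction more than exact size.

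**What to change.** Delete the significance-triggered rule in section 2.12. Before unblinding, name one primary analysis: the risk difference between verum acupuncture plus placebo and itopride plus sham acupuncture, stratified by institution (for example with Mantel-Haenszel weights), with a 95% confidence interval to compare with the -10% margin.

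If covariate adjustment is wanted, list a few prognostic baseline variables in advance (for example baseline NDSI). Fit them in a standardised model that still yields a risk difference, because an odds ratio cannot be compared directly with a margin on the difference scale.

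The cost is one paragraph of text. Institution and the baseline scores are already collected, and the sample size of 57, 67 and 201 stays as it is.
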